### Working Memory: Digit Span test, Verbal N Back

Digit Span: The original digit span task was similar to the Wechsler Memory Scale (24). The participant will be instructed to be attentive to a series of random numbers that will be played once per second. The subject was asked to recall the numbers in reverse order for the digit span backwards (DSB), while the subject was asked to repeat the numbers in a forward series for the digit span forwards (DSF) (25). Each correctly repeated series began with a two-number series and ended with a one-digit series. If the subject failed the first time, they were given another chance with a new set of random numbers for each sequence. If the test subject fails again after the second try, the test will be stopped, as will the longest series they attempt (25).

Verbal N back: Several Indian languages share thirty consonants, which are pronounced one per second. Thirty consonants total, nine of which are repeated (25). The repeated consonants are selected at random. In the 1-back test, the subject responds by tapping the table whenever a consonant is repeated consecutively. In the 2-back test, the subject responds by tapping the table whenever a consonant is repeated after an intervening consonant (26). Scores were based on the number of successes and failures on each test. A negative score was assigned based on the number of errors. After this, the overall score was determined (26).

### Attention: Color Trail Test

The Color Trails Test (CTT): The Color Trail Test is a language-free version of the Trail Making Test (TMT) that was developed to allow for broader cross-cultural application to measure sustained attention in adults (27). Numbered circles are printed with vivid pink or yellow backgrounds that are perceptible to color-blind individuals. For Part 1, the respondent uses a pencil to connect circles rapidly numbered 1–25 in sequence. For Part 2, the respondent rapidly connects numbered circles in sequence but alternates between pink and yellow (28).

### Language: Animal fluency test, COWA

Animal fluency test: The subject will be asked to come up with as many animal names as they can in a minute. The subject is instructed to omit any mention of fish, snakes, or birds. The score was formed by the number of names produced (26).

COWA: Frontal lobe dysfunction can hinder a person’s ability to quickly form words. A typical neuropsychological test for verbal fluency is the Controlled Oral Word Association Test (COWAT), also called the “FAS.” Three-word criteria make up the COWAT. The subject’s objective is to come up with as many words as possible that begin with the specified letter (F, A, or S) in one minute (29). Additionally, subjects are told to avoid using proper nouns, numbers, and the same word with a different suffix (29). Frontal lobe impairment has been successfully detected using the COWAT and other verbal fluency tests. Jerry Janowsky, Arthur Shimamura, and Larry Squire discovered in 1989 that individuals with circumscribed left or bilateral frontal lobe lesions produced noticeably fewer words than control subjects (30).

### Processing Speed: Digit Symbol Substitution

Digit Symbol Substitution: We will administer the DSST to capture processing speed. In this task, participants see a table with a mapping between nine symbols and the digits 1–9. The participants are given 9 seconds to fill in the respective numbers that correspond to the symbols in a large list of symbols. The dependent variable is how many symbols are successfully associated with the respective number (31, 32).

### Quality of Sleep

Pittsburgh Sleep Quality Index (PSQI); Improvement in the quality of sleep using PSQI Score after 6 weeks of intervention (33). The PSQI is a self-reported instrument that measures the quality of sleep as well as sleep disturbances over one month. The scale assesses seven domains: sleep quality, sleep duration, sleep latency, habitual sleep efficiency, sleep disturbances, use of sleep medication, and daytime dysfunction (33).

### Quality of life

World Health Organization Quality of Life (WHOQOL-BREF); improvement in the quality of sleep using the WHOQOL-BREF Score after 6 weeks of intervention. WHOQOL-BREF is a comprehensive tool for assessing quality of life. It was standardized with 26 items and developed by WHO (34). The scale provides a measure of an individual’s perception of quality of life for the four domains: (1) physical health (seven items), (2) psychological health (six items), (3) social relationships (three items), and (4) environmental health (eight items). In addition, it also includes two questions for the ‘overall quality of life’ and ‘general health’ facets. The domain scores are scaled in a positive direction (i.e., higher scores denote a higher quality of life). The range of scores is 4–20 for each domain (34).

### Mini-mental state evaluation score (MMSE)

The MMSE is a measure used for cognitive screening in both clinical and research areas. Scores ≤ 26 on the MMSE indicate the absence of severe dementia (35, 36).

### Genotyping of ApoE ε4

Genomic DNA will be extracted from 2 ml of human whole blood using the NucleoSpin® Blood L kit (Macherey-Nagel) according to the manufacturer’s instructions. Following this, genotyping of ApoE variants will be performed. To perform genotyping, we will use the primers reported by Calero (22). The forward primers are from positions 2886 to 2903, whereas the reverse primers are from positions 3041 to 3058. The polymorphic site contains the 3-end nucleotides, and specific primers will be designed to match one of the two variants at the ApoE positions 2903 and 3041. The primers will be combined in three reaction mixtures that are anticipated to produce an amplification product of 173 bp. These three reaction mixtures are «Reaction ApoE 2» (primers ApoE 112C and ApoE 158C), «Reaction ApoE3» (primers ApoE 112C and ApoE 158R), and «Reaction ApoE4» (primers ApoE 112R and ApoE 158R). Each PCR reaction mixture contained the following: 1× Power SYBR® Green PCR Master Mix (Applied Biosystems), 0.3 M of each primer, and 50 ng of genomic DNA. Negative controls will be performed by using the same reaction mixtures without DNA. All the reactions will be run in duplicate. The PCR amplification protocol would be as reported: initial AmpliTaq Gold DNA Polymerase activation at 95 ◦C for 10 min, followed by 40 cycles with denaturation at 95 ◦C for 15 s, and annealing + extension at 62 ◦C for 1 min. Amplification will be performed either on a 7500 Real-Time PCR System (96-well format) (Applied Biosystems) using the comparative Ct (Ct) method (22).

## Randomization and blinding

A computer-based program will be utilized by a statistician to generate a randomized list. Participants will be randomized by the system into blocks of four, six, eight, or ten, stratified by. Only research staff will be able to retrieve the generated list, which will be kept confidential. The participant will receive the allocation of intervention only after completion of their baseline assessment. Due to the nature of yoga or walking interventions, participants could not be blinded to the intervention allocation. However, outcome assessments will be carried out by blinded.

## Adherence

Adherence will be calculated based on participation in sessions. The trainer will maintain the logbook in Phase 1, while individual participants will receive notepads to keep records in Phase 2. All these will be collected during follow-up assessments. Attendance rates will be calculated by dividing the number of sessions attended by the total number of sessions. Overall attendance will then be calculated by averaging all participants’ attendance rates. Attrition rates will be calculated by dividing the number of individuals who dropped out of the study by the total number of enrolled participants. The reasons cited for study dropout will also be summarized.

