### Study Design

The study DERRY (Dementia Risk Reduction using yoga will be a prospective, parallel-group, single-center, and 2-arm randomized controlled trial wherein the subjects will be randomly allocated to two groups: yoga or active walking control. The protocol has been drafted following the CONSORT guidelines (Consolidated Standards of Reporting Trials) (17) (Figure 1). The study will be conducted between February 2023 and October 2024. A total of 323 adults (aged 30-65 years) with dementia risk (CAIDE score≥6) will be recruited from the community set up through door-to-door surveys and dementia awareness camps across Delhi, India. Eligible participants will be randomized into 1:1 yoga or active control groups. Primary and secondary outcomes will be assessed at baseline (before intervention) and at 24 and 48-week visits (with a 60-day window of flexibility) (see Figure 1). All participants will follow their usual medical regime during the study period. This protocol (RES/IEC-SVYASA/243/2022) has been approved by the Ethics Committee of Swami Vivekananda Yoga Anusandhana Samsthana. Interested and eligible individuals will be asked to attend an orientation session, and informed consent will be obtained from them before participation.

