### Study outcomes and assessments

#### Primary outcome

The primary objective of the study is to assess the efficacy of a yoga intervention vs. brisk walking at 48 weeks on the risk reduction of dementia. The primary endpoint is a difference in the CAIDE risk scores between the yoga and brisk walking groups after 48 weeks (12 months). As shown in CONSORT, assessments will be conducted at baseline, 24 and 48 weeks over 365 days with a 60-day flexibility window (Table 1). However, the primary time endpoint represents a longer-term outcome.

**Table 1 T1:** Schedule of enrolment, interventions, and assessments, according to SPIRIT 2013 guidelines

Time points	Screening Baseline	Intervention	Post-intervention	Endpoint
	week 0+2	24 weeks	24 + 1 week	48 + 1-week
Eligibility screening	x			
Informed consent	x			
Allocation	x			
** *Intervention* **		x		
Yoga/walking		x		
*Yoga*				
Phase I: supervised sessions		x		
Phase II: a synchronized yoga home practice		x	x	
*Control*		x	x	
Brisk walk: Weekly monitoring of daily steps				
*Assessments*				
Demographics and ApoE Genotype	x	x	x	x

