### Intervention

Participants in the yoga group will be given intervention for 6 months, 5 days a week. Intervention would be delivered by qualified yoga professionals (Table 2). The participants will be trained to perform yoga practices by qualified yoga instructors. In the initial orientation at the community center, participants will be given 1 hour for each group-based sessions, which will consist of a 2-minute introduction followed by 10 minutes of gentle loosening movements followed by 1 minute of relaxation, 15 minutes of postures followed by 2 minutes of relaxation, followed by breathing practices of 15 minutes, and end with guided meditation (5 minutes) followed by 3 minutes of relaxation and a 2-minute closing prayer followed by 5 minutes of query and discussion. Overall, the adjunct yoga intervention will be divided into 2 phases: Phase 1, including supervised sessions at the community center, including the orientation; and Phase 2 unsynchronized teleyoga at-home practice (120 sessions) (Table 1). There would be 24 weeks of yoga training followed by asynchronous teleyoga home practice for 24 weekss, 5 days a week.

**Table 2 T2:** Schedule of Yoga Sessions

Yoga Sessions		
	Supervised by Yoga Instructor	Home-Based Asynchronized Teleyoga Practice
Period	Only during Phase I	During Phaes II
Number of sessions	120	120
Duration/ session	60 min	60 min
	Welcome and Philosophical perspective (2 min) Preparatory loosening exercises (10 min) + IRT (1 min) Postural yoga Asanas (15 min) + relaxation (2 min) Breathing exercises: Pranayama (15 min) Guided meditation (5 min) relaxation (3 min) Closing prayer (2 min) Query and discussion (5 min)	Welcome and Philosophical perspective (2 min) Preparatory loosening exercises (10 min) + IRT (1 min) Postural yoga Asanas (15 min) + relaxation (2 min) Breathing exercises: Pranayama (15 min) Guided meditation (5 min) relaxation (3 min) Closing prayer (2 min) Query and discussion (5 min)

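### Adherence records described only for the yoga arm are collected at the follow-up assessments meant to be blinded, and no step keeps them from the outcome assessor

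*Protocol article*

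**What the plan says.** All references are to the protocol article.

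- **Randomization and blinding.** Because of the type of intervention, "participants could not be blinded to the intervention allocation". The safeguard follows: "However, outcome assessments will be carried out by blinded". The sentence stops before naming a role; I read it as meaning blinded outcome assessors.
- **Adherence.** "The trainer will maintain the logbook in Phase 1, while individual participants will receive notepads to keep records in Phase 2". The next sentence fixes when these are gathered: "All these will be collected during follow-up assessments".
- **Intervention and Table 2.** The phases belong to yoga: "Overall, the adjunct yoga intervention will be divided into 2 phases". The first is "Phase 1, including supervised sessions at the community center, including the orientation"; the second is teleyoga practice at home.
- **Primary outcome, Table 1.** Phases I and II appear under the yoga heading. The control entry is "Brisk walk: Weekly monitoring of daily steps", and the Abstract adds weekly telephone contact. Table 1 also marks an adherence row in the post-baseline columns in which CAIDE and most of the cognitive tests are marked.
- **Study Design.** "Primary and secondary outcomes will be assessed at baseline (before intervention) and at 24 and 48-week visits", with 60 days of flexibility.

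**The concern.** In a trial that is open to its participants, blinded assessment is the only stated protection against observer expectation. Here one section sets up that protection, and the next brings records tied to one arm into the same visit. A participant who produces a home-practice notepad is recognisable as a yoga participant. If walkers hand in nothing comparable, its absence is informative too. This route is separate from access to the randomisation list and would remain with a perfectly concealed list.

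At stake is how a positive result can be read. Several cognitive tests leave room for the examiner's judgement or handling. If assessors could see the arm, a difference in favour of yoga could be put down partly to expectation, while the report would still call the assessments blinded.

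**Working it through.** The plan states no figure on this point, so the check sets the sections side by side.

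**1. Do the records identify an arm?** The Adherence section ties the logbook to Phase 1 and the notepads to Phase 2. The Intervention section and Tables 1 and 2 define those phases for yoga alone. Walkers have step monitoring and telephone contact; no phase, logbook or notepad is described for them. On the document's own definitions, a notepad points to yoga.

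**2. Are they present at the blinded visit?** The Adherence section places collection at the follow-up assessments. Study Design puts those at 24 and 48 weeks and has the primary and secondary outcomes measured then. The timing therefore coincides. The collector, the order relative to testing and any separation are not stated.

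**3. At which visits?**

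| Source | Supervised stage | Notepads in use by week 24? |
|---|---|---|
| Intervention, Table 2 | 120 sessions ÷ 5 per week = 24 weeks, then 24 weeks at home | Not at an on-time visit |
| Abstract | 60 contact sessions; 60 ÷ 5 = 12 weeks, if the Intervention section's 5 days a week applies | Yes, possibly from about week 12 |
| Primary outcome, Table 1 | Phase II marked in the 24-week and 24 + 1 week columns (the layout may be damaged in extraction) | Possibly |

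If the 60-day flexibility allows later visits, a week-24 visit could fall up to 60 ÷ 7 ≈ 8.6 weeks into home practice even on the Intervention section's timing. The Phase 1 logbook is held by the trainer, so participants would not be carrying it. By week 48 every version has home practice under way, so notepads are due. Exposure is clear at week 48 and conditional at week 24.

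**4. Which outcomes could an aware assessor influence?**

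- *Cognitive tests (secondary).* N-back scoring counts successes and errors. Animal fluency and COWA require invalid words to be discarded. The Trail Making and Color Trail tests are speeded. Staff administration matters in all of these.
- *CAIDE (primary).* Age, sex, education and ApoE status leave the assessor essentially nothing to shift. Cholesterol is a blood measurement. Physical activity is self-reported by participants who know their arm, so it is open to bias whether or not the assessor is blinded. BMI is measured by staff but leaves little room. Systolic pressure is the main exposed component: it is measured by staff and converted to category points, so a small shift near a boundary can change the score.

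**5. How many participants?** With the plan's 20% attrition, 323 × 0.8 ≈ 258 would remain at week 48, about half of them (129) in yoga. These are ceilings on the number whose arm could be recognised. The figure of 258 also assumes that walkers hand in nothing similar. Neither is an estimate of bias.

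**The case against.** The strongest reply is that the two sections are compatible. The collection sentence is passive and gives a time, not a person. The trainer, a yoga coordinator or the research coordinator could take the records at the same visit without the assessor seeing them. A reader might infer that the assessor necessarily learns the arm at both follow-ups; the document does not support that. No collector is named, the Phase 1 logbook stays with the trainer, and notepads at week 24 depend on the unresolved timing. Nor does the article state that walkers hand in nothing; it only describes nothing for them. All of this stands, and it limits the point to a risk.

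It can also be said that who collects a logbook is operational detail that a journal article leaves to the full protocol. That lowers the weight of the point but does not remove it. The article is not silent: it chooses a collection time, and that time is the blinded visit. The point concerns this stated rule.

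Finally, most of the exposed measures are secondary, and much of CAIDE is beyond an assessor's influence. That also stands.

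**Conclusion.** The point holds as a risk to assessor blinding created by the stated collection rule. It is clear at week 48 and possible at week 24. It bears mainly on the cognitive battery and, within the primary outcome, on systolic pressure. It rests on two readings: that the truncated blinding sentence refers to outcome assessors, and that logbooks and notepads exist only for yoga, as the phase definitions indicate.

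The size of any bias cannot be derived from the document. A reader might be tempted to express a supposed scoring shift as a share of the planned effect, but the article gives neither such a shift nor a numerical effect size. A reader might also infer from the approving ethics committee that the assessors work at a yoga institution; the article does not say who employs them.

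The point changes neither the sample size nor the analysis. It is worth acting on because blinded assessment is the trial's only stated protection against observer bias and the remedy is cheap.

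**What to change.** Replace the collection sentence in the Adherence section with a rule along these lines:

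- The trainer or the research coordinator collects logbooks and notepads, apart from outcome testing. The outcome assessor does not receive or see them.
- Participants are told before each follow-up not to show activity records to assessors and not to disclose their arm.
- The self-reported physical activity item for CAIDE is taken after blood pressure, weight and the cognitive tests, since the answers may themselves suggest the arm.

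The blinding sentence should be completed so that it names the blinded role. The phase timing in the Abstract, Table 1 and the Intervention section must be reconciled; the collection rule above works whichever timing applies.

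The cost is a few sentences and slightly more visit logistics. The trainer and research coordinator are already described in the article, so no new role is needed, provided that whoever collects the records does not also assess outcomes.

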### Intervention

Participants in the yoga group will be given intervention for 6 months, 5 days a week. Intervention would be delivered by qualified yoga professionals (Table 2). The participants will be trained to perform yoga practices by qualified yoga instructors. In the initial orientation at the community center, participants will be given 1 hour for each group-based sessions, which will consist of a 2-minute introduction followed by 10 minutes of gentle loosening movements followed by 1 minute of relaxation, 15 minutes of postures followed by 2 minutes of relaxation, followed by breathing practices of 15 minutes, and end with guided meditation (5 minutes) followed by 3 minutes of relaxation and a 2-minute closing prayer followed by 5 minutes of query and discussion. Overall, the adjunct yoga intervention will be divided into 2 phases: Phase 1, including supervised sessions at the community center, including the orientation; and Phase 2 unsynchronized teleyoga at-home practice (120 sessions) (Table 1). There would be 24 weeks of yoga training followed by asynchronous teleyoga home practice for 24 weekss, 5 days a week.

**Table 2 T2:** Schedule of Yoga Sessions

Yoga Sessions		
	Supervised by Yoga Instructor	Home-Based Asynchronized Teleyoga Practice
Period	Only during Phase I	During Phaes II
Number of sessions	120	120
Duration/ session	60 min	60 min
	Welcome and Philosophical perspective (2 min) Preparatory loosening exercises (10 min) + IRT (1 min) Postural yoga Asanas (15 min) + relaxation (2 min) Breathing exercises: Pranayama (15 min) Guided meditation (5 min) relaxation (3 min) Closing prayer (2 min) Query and discussion (5 min)	Welcome and Philosophical perspective (2 min) Preparatory loosening exercises (10 min) + IRT (1 min) Postural yoga Asanas (15 min) + relaxation (2 min) Breathing exercises: Pranayama (15 min) Guided meditation (5 min) relaxation (3 min) Closing prayer (2 min) Query and discussion (5 min)

The standardized and validated yoga-based intervention module, including çithilikaraa vyäyäma (loosening practices), äsana (postures), pranäyama (breathing practices), and dhyäna (meditation), aimed at bringing harmony to mind and body, will be provided to the participants. While delivering the intervention, the therapist will observe the condition of each subject and make sure to make them understand each practice by adding more explanations to each approach. Modifications will be made individually, according to each participant’s specific limitations. We will be using the previously published module of yoga intervention already reported to reduce cardiovascular risk factors such as high blood pressure and dyslipidemia. The authors reported that using the specific module titled Integrated Yoga Therapy there would be significant improvements in baroreflex sensitivity, systolic blood pressure, and total peripheral vascular resistance in hypertensive patients (37). In a similar vein, Sharma et al. (2020) reported on the management of lipid profiles in patients with coronary artery disease (CAD) using IAYT (38).

We also aim to involve a few strategies to reduce attrition and minimize loss to follow-up based on our prior experiences with yoga-based interventions: (a) being responsive to participants and/or spouse/care partner questions; and (c) the yoga coordinators will meet with participants throughout the study, sometimes traveling to the participant’s fitness facility or home, which should enhance adherence to the program and allow the development of a strong researcher-participant relationship. We have included periodic tele-synchronized sessions as well to decrease the travel burden on participants considering vacations, work commitments, or other reasons influencing adherence to the trial. We have included participants to choose where they exercise and provide the means to do so to promote retention and long-term adherence to exercise. A research coordinator will contact the participants to inquire about their current health status at least once per month.

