**Participants:**

In total, 323 at-risk dementia subjects will be recruited from community settings through health awareness camps and door-to-door surveys across Delhi, India. Participants will be randomized into yoga or brisk-walking groups (1:1). The yoga intervention group will receive 60 contact yoga sessions per 60-min/day at the community parks, followed by continued tele-supervised home practice, further followed by at-home self-practice, and will be tested at 3-time points (baseline, 24-week and 48-week, post-randomization) to test the efficacy of the intervention. The control group will be asked to do brisk walking daily for 45 minutes at their convenience, followed by weekly telephone follow-ups. Applying the intention-to-treat principle, the primary endpoint will be the change from baseline at the 12th month in the Cardiovascular Risk Factors, Aging, and Dementia (CAIDE) Scores. Secondary outcomes will include the composite scores derived from a comprehensive neuropsychology battery, comprising the Trail Making Test, Digit Span Test, N Back, Color Trail, Animal Fluency Test, COWA (Controlled Oral Word Association Test), and Digit Symbol Substitution. The primary outcome will be analyzed using mixed-effect models for repeated measures, adjusted for covariates as fixed effects. The study has been prospectively registered (CTRI/2023/02/049746) on February 15, 2023. The protocol was conceptualized in 2021 and approved by the Institutional Ethics Committee of SVYASA. Recruitment began in February 2023 and is underway with patient enrollment.

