### Statistical analysis

Sample size: A sample size of 269 (n = 135; 135) was derived based on a moderate effect size assumption, using G power software’s formula for F-test, ANCOVA with fixed effect, main effect and main effect interaction model for 2 group comparisons. The calculated sample size also aligns with the estimate presented by Leon et al. 2009 (39). Further, assuming an attrition rate of 20%, the final sample size is n = 323 subjects randomized in a 1:1 ratio to yoga or brisk walking.Baseline characteristics will be presented using appropriate descriptive statistics. Before analysis, variable distributions will be examined to ensure that assumptions of normality are met using statistical software (SPSS, Statistical Package for the Social Sciences, Version 20.0) with the Shapiro-Wilk test. The equivalence of variance will be found using the F distribution test. Depending on the distribution of data, parametric or nonparametric tests will be performed within and between group comparisons for baseline data. The baseline characteristics of the study completers will also be compared with drop-outs. If the data will be skewed, non-parametric analysis through the Kruskal-Wallis test

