Study outcomes will be compared between groups based on the intention-to-treat (ITT) principle. The change in CAIDE risk score from baseline vs. control will be analyzed using a mixed-effects model for repeated measures, adjusted for covariates as fixed effects. The covariates will be the baseline values of the covariates: age (years), education (years), sex (male vs. female), smoking status, and baseline CAIDE risk score. For each continuous endpoint, the baseline of the endpoint variable was included in the model. For genotype x intervention interaction effect, an interaction model will be created, and the influence will be evaluated through a generalized estimated equation model, wherein effect modification by the presence of ApoE 4 allele status will be analyzed by adding the group (yoga vs. walking) x time x variable interaction to the model, together with the main variable effect and variable x time and variable x group interactions. The model will also include interaction terms for treatment by month and a baseline CAIDE risk score by month. IBM SPSS 24.0 software will be used for all statistical analysis. Two-tailed tests will be used, and statistical significance will be set at a p-value < 0.05. Further, assuming an attrition rate of 20% and missing data, we also aim to conduct sensitivity analyses using the multiple imputation method. Subgroup analyses for age, gender, years of education, marital status, socio-economic class, BMI, SBP, Smoking and Alcohol status, etc.

The task of entering data will be carried out by clerical staff who have undergone training in research data entry. All participants will be assigned a participant number, and all data will be stored on an onsite server accessible only to the research team members. A range check will be performed for data values.

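### Yoga is taught in groups and walkers exercise individually, but no class or instructor effect is planned; if outcomes correlate within yoga class, type I error may exceed 5%

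*Protocol article*

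**What the plan says.** Participants are randomised individually, in permuted blocks (Randomization and blinding).

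**Yoga arm.** The Intervention section describes instructor-led teaching. In its sentence on the initial orientation it says that "participants will be given 1 hour for each group-based sessions". Phase 1 is supervised at a community centre. Table 2 gives 120 supervised sessions in Phase I and 120 home sessions in Phase II, and the Adherence section has the trainer keep a logbook in Phase 1. The abstract instead speaks of 60 contact sessions in community parks; these passages need to be reconciled.

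**Walking arm.** The abstract says: "The control group will be asked to do brisk walking daily for 45 minutes at their convenience". Contact is by weekly telephone call, and no grouping is described.

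**Analysis.** The change in CAIDE score "will be analyzed using a mixed-effects model for repeated measures, adjusted for covariates as fixed effects". The listed covariates are age, education, sex, smoking status and baseline CAIDE, and treatment-by-month and baseline-by-month terms are added. No class, instructor or site term appears.

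**Sample size.** "A sample size of 269 (n = 135; 135) was derived based on a moderate effect size assumption", using the G*Power routine for "ANCOVA with fixed effect, main effect and main effect interaction model for 2 group comparisons". No ICC or design effect is mentioned.

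**The concern.** This has the form of a partially nested trial: participants in one arm share a class and a teacher, and those in the other arm do not. Members of one class share the instructor's skill, the pace of teaching and the social pull to attend. Their outcomes may therefore be more alike than those of two yoga participants taken at random. A model that accounts only for repeated visits within a person counts such participants as fully separate pieces of information. Its standard error for the arm contrast is then too small, its confidence interval too narrow and its p-value too low. The sample-size calculation would share the same optimism.

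**Working it through.** **1. The plan's own figures.** 269 × 1.2 = 322.8, which gives the stated 323. The 269 itself cannot be confirmed, because power, the numerical effect size and the numerator degrees of freedom are not given. If moderate is read as f = 0.25 (d = 0.5), a two-group main effect needs 128, 171 or 210 at 80%, 90% or 95% power. That is a separate matter. What counts here is that the stated calculation includes no allowance for classes.

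**2. Inputs.**
- From the Statistical analysis section: "Two-tailed tests will be used" and "statistical significance will be set at a p-value < 0.05"; about 135 evaluable per arm; 1:1 allocation.
- Not in the article, so assumed: class size m, a stable class for each yoga participant, and the ICC of the outcome within class after covariate adjustment.

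**3. Formulas.** With classes in the yoga arm only, equal arms and equal total variance:
- Yoga-arm design effect: DE = 1 + (m − 1) × ICC.
- True over naive variance of the difference: VR = (1 + DE)/2 = [2 + (m − 1) × ICC]/2.
- True over naive standard error: √VR.
- Actual two-sided type I error: 2 × [1 − Φ(1.96/√VR)].

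**4. Numbers put in.**
- m = 10, ICC = 0.01: VR = (2 + 0.09)/2 = 1.045; √VR = 1.022; 1.96/1.022 = 1.92; type I error 5.5%.
- m = 20, ICC = 0.05: VR = (2 + 0.95)/2 = 1.475; √VR = 1.214; 1.96/1.214 = 1.61; type I error 10.7%.

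| m | ICC | VR | True/naive SE | Type I error | Power at d = 0.5, 135 per arm |
|---|---|---|---|---|---|
| any | 0 | 1.000 | 1.000 | 5.0% | 98.3% |
| 10 | 0.01 | 1.045 | 1.022 | 5.5% | 98.0% |
| 10 | 0.05 | 1.225 | 1.107 | 7.7% | 96.0% |
| 15 | 0.01 | 1.070 | 1.034 | 5.8% | 97.8% |
| 15 | 0.05 | 1.350 | 1.162 | 9.2% | 94.2% |
| 20 | 0.01 | 1.095 | 1.046 | 6.1% | 97.5% |
| 20 | 0.05 | 1.475 | 1.214 | 10.7% | 92.3% |
| 30 | 0.05 | 1.725 | 1.313 | 13.6% | 87.9% |

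For m = 10 to 20 and ICC 0.01 to 0.05 the true standard error is 2% to 21% larger than the naive one. Put the other way, the naive one is 1 − 1/1.022 = 2% to 1 − 1/1.214 = 18% too small. Keeping the information of 269 independent participants would need 269 × 1.045 = 281 to 269 × 1.475 = 397.

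**5. Simulation.** 20,000 null trials per setting, about 135 per arm, one endpoint per participant. This is simpler than the planned repeated-measures model. A t-test that ignores classes rejected in 5.4% (m = 10, ICC 0.01) and 10.7% (m = 20, ICC 0.05) of trials, and in 4.9% to 5.1% at ICC 0. An analysis of class means against individual walkers, with Satterthwaite degrees of freedom, rejected in about 5.0% to 5.5% with 7 to 14 classes, and in 5.6% to 6.4% with only 4 classes.

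**The case against.** Several points on the other side have force.

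- *The inflation is not established.* A reader might infer that the standard errors are too small and that the type I error does exceed 5%. The article does not support that: it gives neither class size nor ICC, and at ICC 0 the error is 5.0%. This stands, so the conclusion is conditional.
- *Independence is never stated.* A reader might also infer that the model treats all participants as independent. The random effects are not listed, and an analysis plan that is not shown could include a class term. This stands in part. The article does list covariates and interaction terms in detail without class or instructor, and a fixed-effect ANCOVA sizing rests on independent observations.
- *Group teaching is explicit only for the orientation.* Group delivery throughout Phase 1 and stable class membership are inferences. The article also describes individual modifications, some tele-sessions, visits by coordinators and a choice of where to exercise. This stands, and it affects which clustering unit fits.
- *The endpoint is remote from the classes.* The primary comparison at 48 weeks follows 24 weeks of home practice, so class effects may have faded. They need not have vanished, and the 24-week visit in the same model closes the supervised phase.
- *CAIDE has fixed components.* Sex, education and ApoE status cannot change, so the concern does not reach every secondary outcome. The force for the primary endpoint is limited, because it is a change adjusted for baseline and comes mainly from blood pressure, BMI, cholesterol and reported activity.
- *Shared location.* Neighbourhood effects common to both arms do not inflate the error of the contrast under individual randomisation; effects specific to a yoga class or instructor do.

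**Conclusion.** The concern holds in conditional form. Yoga has a shared teaching structure that walking lacks, and neither the stated model nor the sample size allows for it. If the within-class ICC is positive, the standard error of the primary contrast is understated. With stable classes of 10 to 20 and an ICC of 0.01 to 0.05, type I error would be about 5.5% to 10.7%. These ranges are assumptions, and the true figure may lie near the lower end or at 5.0%, particularly at 48 weeks. The cost in power is modest if the true effect is d = 0.5: from about 98% to between 92% and 98%. The main reason to act is protection of the type I error. This is a worthwhile improvement to the plan; it is not evidence that the planned result would be invalid.

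**What to change.** - Record class and instructor for every yoga participant, for example in the Phase 1 trainer logbook, including any change of class. Membership that is not recorded at the time may be hard to recover.
- Add a random intercept for class in the yoga arm only, with each walker as a cluster of one and Satterthwaite degrees of freedom. Use instructor instead if classes are not stable. Apply this to the primary outcome and to those secondary outcomes that can change. At minimum, prespecify it as a sensitivity analysis.
- Report the ICC, preferably at both 24 and 48 weeks, since home practice lies between them.

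The cost is one or two recorded variables and one model term. Under the assumptions above, intervals would be roughly 2% to 21% wider, with little or no change if the ICC is near zero. With very few classes the correction is imperfect, as the 4-class simulation shows, so the number of classes should be reported too.
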